### Procedure

The current study takes place within the Dutch specialized mental health care setting and is a multicenter trial. Patients are recruited via Pro Persona mental health care (four locations: Arnhem, Ede, Nijmegen, Tiel), the Radboud University Medical Center (Nijmegen), and GGNet Network for mental health care (location Zutphen). If patients are eligible for participation, the therapists approach them for the study and they are contacted by a researcher. Study information is provided via a letter. Patients are contacted again after at least 48 h to discuss participation and answer any remaining questions. If patients decide to participate, they are asked to sign the informed consent form and are then randomized to either the gcSC condition or the gcSC with adjunct exercise treatment condition. The participant flow is depicted in Fig. 1.

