**Fig. 1 Fig1:**
[figure not shown]
CONSORT flow chart

Patients in the gcSC with adjunct exercise condition start the exercise treatment simultaneously to the gcSC treatment (with a maximum two-week difference between start dates). Patients complete the baseline assessment in the week before the first treatment session. The surveys are sent via email using the online cloud-based data solution program, Castor EDC and can be filled out via any personal device (e.g. computer, tablet). This program is also used for the Case Report Forms and initial data management. Additionally, patients receiving the adjunct exercise treatment fill out a short questionnaire before and after each supervised exercise session on paper, as part of the treatment. An overview of the assessments can be found in Table 1 and Fig. 1. Expected study duration is 36 months. Inclusion of patients started in March 2020.

**Table 1 Tab1:** Assessment schedule

		Time point								
Endpoints	Material	T0	T1	T2	T3	T4	T5	T6	T7	T8
Primary outcome	IDS-SR	X	X	X	X	X	X	X	X	X
Secondary outcomes	SCID-5-S					X	X	X	X	X
	IPAQ	X	X	X	X	X	X	X	X	X
	Fitness^a^	X				X				
	WHODAS	X				X				X
	MEI-SF	X				X				X
Economic evaluation	EQ-5D-5L	X				X	X	X	X	X
	Tic-P	X				X	X	X	X	X
Mechanisms	RRS	X	X	X	X	X	X	X	X	X
	RSES	X	X	X	X	X	X	X	X	X
	SRET	X				X				X

^a^Assessed in 15% of randomly selected patients from both conditions

*IDS-SR* Inventory of Depressive Symptomatology (i.e. depressive symptoms)*, SCID-5-S* Structured Clinical Interview for DSM-5 (i.e. depressive remission), *IPAQ* International Physical Activity Questionnaire (i.e. physical activity), *WHODAS* World Health Organization Disability Assessment Schedule (i.e. disability), *MEI-SF* Motivation and Energy Inventory-Short Form (i.e. motivation and energy), *EQ-5D-5L* (i.e. quality of health), *Tic-P* Trimbos Institute and iMTA Cost questionnaire for Psychiatry (i.e. economic costs), *RRS* Ruminative Response Scale (i.e. rumination), *RSES* Rosenberg Self-Esteem Scale (i.e. self-esteem), *SRET* Self-Referent Encoding Task (i.e. memory bias)

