### Material

#### Depressive symptoms

To assess the severity of depressive symptoms, as primary outcome of the RCT, the Dutch version of the Inventory of Depressive Symptomatology-Self Report (IDS-SR) [62] is used. This scale consists of 30 items, measuring the severity of different depressive symptoms on a four-point Likert scale. Validity and reliability have been established, with Cronbach’s alpha ranging between 0.76 and 0.82 in depressed outpatients [62].

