#### Remission

The clinician-rated Structured Clinical Interview for DSM-5 (SCID-5-S) [63] is used to assess clinically defined remission at follow-up. The SCID-5-S is administered over the phone by trained and blinded assessors, conform recommendations [25]. The Dutch version was shown to have moderate to excellent inter-rater agreement of the Axis I disorders [64].

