### Statistical analysis

Given the ongoing advances in statistics and technology, all analyses will be performed in line with best current practice. Following the CONSORT statement [78], all our analyses will adhere to the intention-to-treat (ITT) principle (i.e., with an analysis of all patients as randomized). To this end, analyses of treatment effects will be conducted with multilevel mixed modelling, with treatment condition as factor and the depended measure as baseline covariate, while missing observations will be multiply imputed (with chained equations) for the health-economic analyses. In addition, we will also report the results in the per-protocol sample (≥ 6 supervised exercise sessions). Generalized (logit) mixed modelling will be used to compare the conditions on number of patients in remission at each follow-up measure. To examine whether rumination, self-esteem and memory bias are the mechanisms of change between adjunct exercise treatment and a decrease in depressive symptoms, multilevel structural equations modelling will be performed in Stata [79], or alternatively Hayes’ PROCESS macro [80] for SPSS [81] will be used.

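### The self-reported baseline appears to be collected after randomisation, probably with the arm known, yet it is the covariate in the treatment-effect mixed models

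*Protocol article*

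**What the plan says.** The Procedure section sets out the order of entry. Once a patient agrees to take part, "they are asked to sign the informed consent form and are then randomized to either the gcSC condition" or to the exercise arm. No assessment is mentioned between signature and allocation.

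The text after Fig. 1 places T0 relative to treatment, not to randomisation: "Patients complete the baseline assessment in the week before the first treatment session". It also says that exercise patients "start the exercise treatment simultaneously to the gcSC treatment (with a maximum two-week difference between start dates"), and describes the mode of collection: "The surveys are sent via email using the online cloud-based data solution program, Castor EDC".

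For the primary outcome, "the Dutch version of the Inventory of Depressive Symptomatology-Self Report (IDS-SR) [62] is used" (Depressive symptoms section). It is self-reported at T0 and at every later time point in Table 1. Blinding is stated only for the SCID-5-S, which is "administered over the phone by trained and blinded assessors" (Remission section).

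The Statistical analysis section commits to analysing all patients as randomised. It fits multilevel mixed models "with treatment condition as factor and the depended measure as baseline covariate". Multiple imputation is named only for the health-economic analyses.

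**The concern.** Adjusting for baseline is safe when allocation cannot have influenced the baseline. Here nothing in the text protects it. An exercise programme cannot be masked from the patient, and gcSC patients are offered it only after follow-up ends. The Strengths and limitations section itself expects volunteers to be favourably disposed to exercise. Hope in one arm or disappointment in the other could therefore colour self-reported T0 scores, and the model would treat that difference as a chance pre-treatment imbalance and adjust for it.

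Two things are at stake. The adjusted effect can be biased by an amount that a larger sample does not reduce. And a patient who withdraws after randomisation but before T0 has no covariate value. A standard mixed model copes with missing outcomes, but not with a missing baseline covariate.

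**Working it through.** **Order of steps.** The text gives consent, then randomisation, then (in a separate paragraph, after the arms have been named) T0 in the week before first treatment. Exercise has to be arranged to start alongside gcSC, so the arm must be known when the first session is booked. No sentence places T0 before randomisation. Allocation before T0 is the natural reading, but it is an inference.

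**Inputs from the Sample size calculation section.** Effect 0.70 (SD = 1), two-sided α = 0.05, 60 per arm, mean cluster size 10 (range 5 to 15), intra-cluster correlation 0.05, design effect 1.48, baseline to follow-up correlation r = 0.30.

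**Check of the plan's figures.** Reading the range as four SDs gives a coefficient of variation of 2.5/10 = 0.25. The design effect is then 1 + ((0.25² + 1) × 10 − 1) × 0.05 = 1.48, as stated. The 60 per arm is not reproduced: 33 × 1.48 × (1 − 0.30²) = 44.4 per arm. That gap is on the safe side and has no bearing on this point.

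**Assumption.** The documents give no size for an allocation-induced T0 shift s. I take s = 0.1, 0.2 and 0.3 SD, with none of it carrying over to follow-up.

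**Bias.** The adjusted effect is the follow-up difference minus slope × T0 difference. With equal SDs the slope is about r, so the bias is about r × s.

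**Power.** Effective n per arm = 60/1.48 = 40.5. The residual SD is √(1 − 0.30²) = 0.954, and the standard error is 0.954 × √(2/40.5) = 0.212. Power is Φ(effect/0.212 − 1.96).

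| s (assumed) | Bias at r = 0.30 | Effect if attenuated | Power |
|---|---|---|---|
| 0 | 0 | 0.70 | 0.910 |
| 0.1 | 0.03 | 0.67 | 0.885 |
| 0.2 | 0.06 | 0.64 | 0.856 |
| 0.3 | 0.09 | 0.61 | 0.821 |

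**More persistent measures.** If r were 0.50 (assumed), the bias would be 0.05 to 0.15 SD. If r were 0.70 (assumed), it would be 0.07 to 0.21 SD.

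**Direction.** If hope lowers T0 symptoms in the exercise arm, or disappointment raises them in gcSC, the exercise arm has the lower T0 score in both cases. The model credits part of its later advantage to that, so the estimated benefit shrinks. A shift the other way would enlarge it.

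**The case against.** The strongest reply is that the order is never stated. The article refers the reader to Fig. 1 for the participant flow, and the figure is not in the copy reviewed. Tying T0 to the first treatment session is compatible with either order. This stands: a reader might take it as established that T0 follows randomisation and that patients know their arm when they complete it, but the documents do not say either. They do not say when patients are told. What remains is that the text as written does nothing to prevent it.

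A reader might also infer that every analysis is affected. The documents do not support that. The covariate sentence covers the treatment-effect mixed models. For remission, "Generalized (logit) mixed modelling will be used to compare the conditions on number of patients in remission at each follow-up measure": no baseline covariate is named, and Table 1 has no SCID-5-S at T0. None is named for the mediation or health-economic analyses either. T0 utility may enter the QALY, but its weight is small. Under a trapezoid rule (assumed), with T4 at about 12 weeks, T0 carries (12/52)/2 = 0.115 years, so an assumed utility shift of 0.05 moves the QALY by about 0.006.

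On intention-to-treat, how a missing baseline is handled is commonly left to an analysis plan that is not shown. It therefore cannot be said that such patients will be excluded, only that they would lack the covariate. Selective loss of disappointed gcSC patients is conjecture.

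Finally, tying T0 to treatment start keeps the baseline current. That is a real advantage, and the fix has to respect it.

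**Conclusion.** The point holds as a weakness in the described sequence, of modest size. The self-reported baseline appears to be taken after allocation and probably with the arm known, and the treatment-effect models condition on it.

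At the protocol's r = 0.30 the bias in the primary effect is about 0.03 to 0.09 SD against an assumed effect of 0.70, and power at 60 per arm stays at or above 0.82. This rests on an assumed shift of 0.1 to 0.3 SD that has gone by follow-up. Measures with higher persistence would be affected more.

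A reader might infer that the trial risks a false claim of benefit. The documents do not support that: under the mechanism that makes a shift plausible, the bias runs toward the null. The case for acting is that the bias route is avoidable at almost no cost, not that the primary result is in serious danger.

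**What to change.** - **Patients still to be enrolled:** make completion of T0 in the data system a condition for randomisation, so that the order is consent, T0, randomisation, treatment. If that is not feasible, complete T0 at least before the arm is disclosed. That protects the scores, but does not guarantee a baseline for everyone randomised.
- **Patients already randomised before T0** (inclusion began in March 2020): add a sensitivity analysis without the T0 covariate, adjusting for the stratification factors gender and setting.
- **If T0 already precedes randomisation in practice:** correct the Procedure section to say so, and state when patients learn their arm.

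**Cost.** The surveys are already online, so the change reorders two steps. The small downside is an older baseline when treatment start is delayed, which calls for a short validity window for T0. The sensitivity analysis gives up a little precision: on the stated inputs, power at 60 per arm is 0.883 without baseline adjustment, against 0.910 with it. The sample size does not change.

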**Fig. 1 Fig1:**
[figure not shown]
CONSORT flow chart

Patients in the gcSC with adjunct exercise condition start the exercise treatment simultaneously to the gcSC treatment (with a maximum two-week difference between start dates). Patients complete the baseline assessment in the week before the first treatment session. The surveys are sent via email using the online cloud-based data solution program, Castor EDC and can be filled out via any personal device (e.g. computer, tablet). This program is also used for the Case Report Forms and initial data management. Additionally, patients receiving the adjunct exercise treatment fill out a short questionnaire before and after each supervised exercise session on paper, as part of the treatment. An overview of the assessments can be found in Table 1 and Fig. 1. Expected study duration is 36 months. Inclusion of patients started in March 2020.

**Table 1 Tab1:** Assessment schedule

		Time point								
Endpoints	Material	T0	T1	T2	T3	T4	T5	T6	T7	T8
Primary outcome	IDS-SR	X	X	X	X	X	X	X	X	X
Secondary outcomes	SCID-5-S					X	X	X	X	X
	IPAQ	X	X	X	X	X	X	X	X	X
	Fitness^a^	X				X				
	WHODAS	X				X				X
	MEI-SF	X				X				X
Economic evaluation	EQ-5D-5L	X				X	X	X	X	X
	Tic-P	X				X	X	X	X	X
Mechanisms	RRS	X	X	X	X	X	X	X	X	X
	RSES	X	X	X	X	X	X	X	X	X
	SRET	X				X				X

^a^Assessed in 15% of randomly selected patients from both conditions

*IDS-SR* Inventory of Depressive Symptomatology (i.e. depressive symptoms)*, SCID-5-S* Structured Clinical Interview for DSM-5 (i.e. depressive remission), *IPAQ* International Physical Activity Questionnaire (i.e. physical activity), *WHODAS* World Health Organization Disability Assessment Schedule (i.e. disability), *MEI-SF* Motivation and Energy Inventory-Short Form (i.e. motivation and energy), *EQ-5D-5L* (i.e. quality of health), *Tic-P* Trimbos Institute and iMTA Cost questionnaire for Psychiatry (i.e. economic costs), *RRS* Ruminative Response Scale (i.e. rumination), *RSES* Rosenberg Self-Esteem Scale (i.e. self-esteem), *SRET* Self-Referent Encoding Task (i.e. memory bias)

### Ethics

The present study was approved by the Medical Ethics Committee of Arnhem-Nijmegen (under the registration code: NL72080.091.19) and is registered within the Netherlands Trial Register (code: NL8432). Because recently self-esteem was found to be a possible mechanism of change of exercise treatment [35], we decided to include a self-esteem measure after preregistration. All data will be processed in a confidential manner and data is processed using an identification code with only the principal investigator (PI) and the coordinating investigators (CI) having access to the key. The research process is regularly monitored by a trained and independent monitor, which includes monitoring of the completeness of informed consents, data safety, and correspondence with the ethics committee. Serious adverse events will be reported to the Medical Ethics Committee, although none are expected due to the low-risk intervention.

### Randomization

Randomization is stratified for gender and setting, using Castor EDC. This program consecutively enrolls patients in line with a four, six and eight block design. These blocks are created for both strata separately. The first block is generated with the first randomization and thereafter a new block is randomly selected and generated when the previous one is used up. Allocation of patients is randomly selected from the block in use. More information on the randomization algorithm can be found on the website of Castor EDC.^1^

### Interventions

***gcSC.*** The gcSC treatment is delivered in line with the Dutch multidisciplinary guidelines for depression treatment, consisting of pharmacological and/or psychological interventions which are offered individually or in group format.^2^ The gcSC condition may also receive some form of body-oriented or physical activity treatment but no prescribed exercise treatment.

#### Adjunct exercise

Patients receiving the adjunct exercise treatment, exercise once a week under supervision of psychomotor therapists or trained nurses and commit to exercising twice a week at home for 12 weeks. Supervised exercise generally consists of running or indoor cycling (spinning), which are usually both offered in a group setting, although other exercise types and individual supervised exercise are also provided. The exercise sessions last for 45 min at moderate intensity, which is based on heart rate frequency (i.e. *moderate = 64–76% of HRmax = 220 – age)*. This kind of exercise intervention is evidence-based and recommended by the National Institute for Health and Care Excellence (NICE) [61]. Patients track the intensity, duration, and frequency of each exercise session, with the aid of a non-invasive activity tracker (Fitbit)^3^ which is provided for the length of the study (i.e. 15 months).

### Material

#### Depressive symptoms

To assess the severity of depressive symptoms, as primary outcome of the RCT, the Dutch version of the Inventory of Depressive Symptomatology-Self Report (IDS-SR) [62] is used. This scale consists of 30 items, measuring the severity of different depressive symptoms on a four-point Likert scale. Validity and reliability have been established, with Cronbach’s alpha ranging between 0.76 and 0.82 in depressed outpatients [62].

#### Remission

The clinician-rated Structured Clinical Interview for DSM-5 (SCID-5-S) [63] is used to assess clinically defined remission at follow-up. The SCID-5-S is administered over the phone by trained and blinded assessors, conform recommendations [25]. The Dutch version was shown to have moderate to excellent inter-rater agreement of the Axis I disorders [64].

#### Physical activity and fitness

To assess self-rated physical activity level, the Dutch version of the International Physical Activity Questionnaire (IPAQ) [65] is used. Psychometric properties of this questionnaire were shown to be acceptable in different settings and populations [66]. Moreover, to assess objective physical activity level and heart rate, patients receive the Fitbit in the adjunct exercise intervention condition, as it allows self-dosing during the exercise sessions, enables patients to learn how to effectively exercise to counteract depression, and helps patients motivate themselves, hence contributing to adherence. Additionally, to objectively assess physical fitness, fitness tests will be conducted at baseline and after the 12 weeks of exercise or gcSC treatment in 15% of the sample (selected at random). Here, the main endpoint is improvement in cardiorespiratory fitness.

#### Mood

Patients provide a positive and negative mood rating (on Visual Analogue Scales) directly before and after each supervised exercise session. They are encouraged to also use the mood ratings at home to monitor direct mood benefits. This is a technique used in clinical practice, to motivate patients to engage in exercise [67] and can thereby contribute to adherence and long-term exercise [68].

#### At-home exercise

Embedded in the same questionnaire as the mood ratings, patients indicate the type, frequency, duration, and intensity (mean and peak heart rate, as indicated by the Fitbit) of the previous two weekly at-home sessions. The psychomotor therapists/nurses discuss how the week went and together with the patient adapt the personalized exercise plan if needed. To motivate patients, different strategies are used that are integrated in the personalized plan. These strategies are based on previous research [67, 68] and psychomotor clinical practice and include psychoeducation, weekly exercise session scheduling, and goal setting.

#### Disability

Disability is assessed with the Dutch version of the World Health Organization Disability Assessment Schedule (WHODAS 2.0) [69]. Thirty-six items are designed to measure functioning in different domains on a five-point Likert scale, ranging from 0 (i.e. no effort at all) to 4 (i.e. much effort). Reliability and validity of the scale are established for different populations [69].

#### Motivation and energy

To assess motivation and energy, the Motivation and Energy Inventory-Short Form (MEI-SF) [70] is used. The MEI-SF was translated into Dutch and then back-translated into English by bilinguals from the University of Texas at Austin. On 18 items, this scale measures the level of motivation and energy using seven-point Likert scales, ranging from 0 (i.e. none of the time) to 6 (i.e. all the time). This scale was specifically developed to evaluate interventions designed to improve motivation and energy in depressed patients. In previous research, Cronbach’s alpha ranged between .86 and .94 at baseline and .95 and .96 at the end of study, indicating high internal consistency [70].

#### Health-related quality of life

For the health-economic evaluation, changes in patients’ health-related quality of life are assessed with the EuroQol’s 5-level version, the EQ-5D-5L (https://euroqol.org) in combination with the Dutch tariff [71]. Patients indicate their health state on different domains (i.e. mobility, self-care, usual activity, pain/discomfort and anxiety/depression), which is then transformed into a health state valuation (a utility score) which is anchored between 0 (i.e. dead) and 1 (i.e. perfect health). The utility is used to calculate the quality-adjusted life-years (QALY) over the studies follow-up time. Hence, the length of time spend in a particular health state is weighed by the utility score to obtain the QALY.

#### Healthcare costs

and costs stemming from productivity losses are assessed with the Trimbos Institute and iMTA Cost questionnaire for Psychiatry (Tic-P) [72] which measures resource use such as use of health services, patients’ and their family’s out-of-pocket costs, and lesser productivity owing to absenteeism and work cutback (presenteeism).

#### Rumination

Rumination is measured using the Dutch version of the Ruminative Response Scale (RRS) which was shown to be a valid and reliable tool for this purpose [73]. This scale consists of 26 items which are rated on four-point Likert scale, ranging from 0 (i.e. almost never) to 3 (i.e. almost always).

#### Self-esteem

Self-esteem is assessed using the Dutch version of the Rosenberg self-esteem scale (RSES) [74]. Global self-esteem is measured with ten items on a four-point Likert scale, ranging from 0 (i.e. strongly disagree) to 3 (i.e. strongly agree). Psychometric properties of the Dutch version were established, with a one-factor solution and high internal consistency [75].

#### Memory bias

To measure memory bias, the computerized Self-Referent Encoding Task (SRET) [76] is used. This task is a reliable method to assess memory bias [76, 77]. During the encoding phase, twelve positively and twelve negatively valenced adjectives are presented on the computer screen, one by one. No more than two words of the same valence are presented sequentially. Patients make a categorical decision whether the adjective is self-descriptive or not, by pressing on either of two keyboard buttons. After a 2 min distraction task (i.e., the Trail Making Test), the patients have 3 min to type in all the words they can remember from the previous task. Spelling errors are permitted.

